**Objective:**

The CONFUSED study aims to identify molecular and clinical predictors of POD by integrating clinical data with proteomic, transcriptomic, and epigenetic analyses. The primary objective is to develop predictive models for POD using multimodal data. Secondary objectives include the identification of delirium-associated genes, proteins, and epigenetic signatures, as well as the exploration of patient subgroups at increased risk for POD.

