Given the limited sample size relative to the high-dimensional omics data, all predictive models are exploratory and hypothesis-generating. External validation in independent cohorts will be necessary to confirm predictive performance and clinical utility. Models trained on clinical variables alone will be benchmarked alongside multiomics models for exploratory comparison, reflecting potential applicability in settings where omics data are not routinely available.

The final operating threshold will be selected to prioritize either sensitivity (screening scenario) or specificity (confirmatory setting), as dictated by the clinical use case. Alongside the integrative models, versions limited to routinely available clinical variables will be trained and benchmarked to ensure bedside applicability where omics data are not regularly available. To interpret the resulting models, feature-attribution techniques such as SHAP (Shapley Additive Explanations) values will quantify and visualize each variable’s influence on the prediction, thereby generating mechanistic hypotheses about the molecular and functional pathways leading to POD. To clarify the clinical deployment strategy, the study is designed to yield 2 distinct and complementary model types. The first is a purely preoperative clinical model, trained exclusively on variables available at the preanesthesia outpatient clinic, specifically the DRAS, Mini-Mental State Examination score, age, comorbidities, surgical type, and medication profile. This model requires no blood sampling and can generate a risk prediction at the time of the outpatient consultation, typically days to weeks before surgery. This is the primary bedside instrument of the study and the relevant window for initiating preventive measures, including medication review and reduction of anticholinergic burden, sleep hygiene counseling, optimization of sensory aids, cognitive stimulation, and planning of early postoperative mobilization. The second is an integrative multimodal model incorporating longitudinal biomarker data from all 4 perioperative collection time points. This model serves a distinct purpose: continuous refinement of risk estimates throughout the hospital stay, enabling early detection of evolving POD in the postoperative period. Postoperative biomarker data are therefore not a prerequisite for preoperative risk stratification but an additional layer extending clinical utility into the postoperative setting.

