### Comparison With Existing POD Prediction Models

Several prediction models for POD have been developed over the past decade, including the Validation of Prediction of Delirium in ICU Patients (PRE-DELIRIC) model, models based on inflammatory biomarkers, and preliminary ML approaches using single-omics or clinical variables. These models have provided important insights into POD risk factors, but they are generally limited by reliance on either clinical variables alone or a single biomarker modality and often do not account for the complex, multifactorial pathophysiology of delirium.

The CONFUSED study aims to extend beyond these approaches by integrating multiple layers of omics data—proteomics, transcriptomics, and epigenetics—with detailed clinical variables. This integrative, multimodal approach allows for the identification of candidate biomarker signatures and mechanistic pathways associated with POD, which cannot be captured by single-omics or clinical-only models. Advanced ML techniques, including feature selection, regularization, and nested cross-validation, are applied to ensure robustness and interpretability of exploratory predictive patterns.

While this study does not yet provide a systematic performance comparison with existing POD prediction models, it is designed to generate hypotheses and candidate signatures that can inform future external validation studies. By combining diverse molecular and clinical data with interpretable ML, the CONFUSED study seeks to provide incremental value in understanding POD risk and to lay the groundwork for the development of more comprehensive and mechanistically informed predictive models.

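### The two named models differ in both data type and time window, and no preoperative clinical-plus-omics model is named, so the plan does not commit to estimating what biomarkers add to early prediction

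*Protocol article*

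**What the plan says.** All references are to the protocol article.

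- **Aim.** In the Abstract, under Objective: "The primary objective is to develop predictive models for POD using multimodal data". The Abstract's Background gives the motivation as the absence of reliable biomarkers for predicting delirium early and preventing it. The section Comparison With Existing POD Prediction Models adds that "the CONFUSED study seeks to provide incremental value in understanding POD risk".
- **Models.** Integrative Data Analysis and AI Model Development says "the study is designed to yield 2 distinct and complementary model types". One of the two relies on clinical data alone, being "a purely preoperative clinical model, trained exclusively on variables available at the preanesthesia outpatient clinic", and the text adds about its use: "This model requires no blood sampling and can generate a risk prediction at the time of the outpatient consultation". The other is multimodal, takes biomarker data from all four perioperative draws, and is meant to refine risk during the stay and pick up delirium as it develops. Clinical Data Collection and Processing calls it the integrative postoperative model.
- **Benchmark.** Two sentences in the same analysis section cover it: "Models trained on clinical variables alone will be benchmarked alongside multiomics models for exploratory comparison" and "Alongside the integrative models, versions limited to routinely available clinical variables will be trained and benchmarked". Neither gives a time window.
- **Data.** The Abstract and Blood Sampling and Analysis place one draw before surgery and three after it (immediately postoperative, day 2, day 5). Table 1 lists microarray, epigenetic, genotyping and proteomic work at baseline.

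**The concern.** The study's motivation is biomarkers for early prediction, and the article itself identifies the preoperative clinic visit as the window in which prevention can start. The molecular question that follows is whether the preoperative sample improves on what the clinic already knows at that point. Neither named model answers it: one excludes blood, and the other includes three postoperative draws.

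If the two are set side by side, the omics model may do better because molecular data carry predictive information, or because it has seen the patient after surgery, when some delirium may already have begun. A favourable gap could then be taken as evidence for a preoperative biomarker panel and carried into the external validation and lower-cost assays that the article foresees.

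**Working it through.** The plan states no figure for this comparison, so there is none to reproduce. The check has two parts.

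**1. Lay the models out by data type and time.**

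| | Preoperative only | Through day 5 |
|---|---|---|
| Clinical only | First model type (named) | Possibly the clinical-only versions; window not stated |
| Clinical plus omics | Not named | Second model type (named) |

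The two named types sit on the diagonal, so their difference changes both factors. The contrast for early prediction is the left column: clinical plus omics minus clinical only, both preoperative. One of its two cells is missing. Filling the upper-right cell with a time-matched clinical version would isolate the omics contribution after surgery, but would leave the left column incomplete.

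**2. Illustrate the size.** All effect sizes here are assumptions; none comes from the article.

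- Clinical score: normal with equal variance in both groups, mean shifted by 0.74 SD in delirium cases. AUC = Φ(0.74/√2) = Φ(0.523) = 0.700.
- A marker independent of the clinical score within outcome groups, shifted by *d* SD. The best linear combination has a shift of √(0.74² + *d*²), so AUC = Φ(√(0.74² + *d*²)/√2).
- *d* = 0.5: √(0.5476 + 0.25) = 0.893; Φ(0.893/√2) = Φ(0.632) = 0.736; gain 0.037.
- *d* = 1.0: √(0.5476 + 1) = 1.244; Φ(1.244/√2) = Φ(0.880) = 0.810; gain 0.111.

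A simulation of 400,000 patients with 24% delirium agrees to within 0.001:

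| Shift of preoperative marker (SD) | Shift of postoperative marker (SD) | Clinical, preoperative | Clinical plus omics, preoperative | Clinical plus omics, all four draws | Gap between the two named types | True preoperative gain |
|---|---|---|---|---|---|---|
| 0 | 0.5 | 0.699 | 0.699 | 0.735 | 0.036 | 0.000 |
| 0 | 1.0 | 0.699 | 0.699 | 0.810 | 0.111 | 0.000 |
| 0.5 | 0 | 0.699 | 0.736 | 0.736 | 0.037 | 0.037 |

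The first and third rows give practically the same gap between the named models, yet the preoperative sample is worthless in one and useful in the other. Only the model that is not named separates them (0.699 against 0.736).

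**The case against.** The case against has several parts.

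- **The article never says the two model types will be compared with each other.** They are introduced as a deployment strategy with different purposes, and the clinical comparator in the benchmark may be the integrative model with the omics removed, over the same period. This stands. A reader might infer that the planned benchmark itself confounds data type with time; the text does not establish that, because it gives no window. The confounding is certain only for the two named types.
- **The preoperative sample exists, so the question can be answered.** This also stands. A reader might infer that the design rules out an answer. It does not; the plan only fails to commit to the analysis that would give one.
- **The primary objective is to develop multimodal models, not to estimate incremental preoperative discrimination, and everything is labelled exploratory.** Correct as to wording, and the phrase about incremental value concerns understanding of risk, not AUC. But the article's own rationale is early prediction, and an exploratory contrast still has to isolate the quantity of interest to guide later validation.
- **Feature sets and fold details belong in an analysis plan that is not shown.** True of folds, intervals and reference scores. The point does not rest on those. It rests on the article's own definition of the two model types, one of which excludes blood while the other is labelled postoperative.
- **Delirium Risk Assessment Score (DRAS) as a comparator.** A score of at least 5 is an inclusion criterion, so its range is restricted and it would look weak here. It is not a required benchmark.

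**Conclusion.** The concern holds in a limited form. The two named model types differ in data type and in time, no preoperative clinical-plus-omics model is named, and the benchmark has no stated time window. A gap between the named types cannot be read as the value of biomarkers for early prediction, and the plan does not commit to estimating that value. Time-matched clinical-only versions through day 5 would not change this.

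For size, an apparent gain of about 0.04 to 0.11 AUC can arise with zero preoperative gain. This assumes a clinical AUC of 0.70, one conditionally independent marker and a postoperative shift of 0.5 to 1 SD; another baseline AUC or shift would change it. A reader might infer a larger figure by setting a reactive marker on its own against chance: a 1 SD shift gives Φ(1/√2) = 0.76 against 0.50. That is not the gain over a clinical model and should not be used here.

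The change is worth making before final data lock. The models are declared exploratory, which limits the harm but does not make the contrast interpretable.

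**What to change.** 1. Add one model: preoperative clinical variables plus omics from the preoperative sample.
2. State the time window of every model in the benchmark. At each sampling time, compare clinical-only with clinical-plus-omics in the same patients and the same outer folds, with both sides using only data available by then. Delirium assessments are listed among the clinical inputs, so say whether they enter, and treat them identically on both sides.
3. Report paired differences in performance (for example AUC and Brier score) with 95% CIs, and report the preoperative pair explicitly, labelled exploratory.
4. Say that the difference between the two deployment models is not an estimate of omics value.
5. Optionally show the DRAS alone as a reference in the same folds, with the caveat about its restricted range.

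Cost: about a paragraph of text and extra model fits on data already being collected. The downside is that the omics gain will probably look smaller and its interval will be wide.

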### Comparison With Existing POD Prediction Models

Several prediction models for POD have been developed over the past decade, including the Validation of Prediction of Delirium in ICU Patients (PRE-DELIRIC) model, models based on inflammatory biomarkers, and preliminary ML approaches using single-omics or clinical variables. These models have provided important insights into POD risk factors, but they are generally limited by reliance on either clinical variables alone or a single biomarker modality and often do not account for the complex, multifactorial pathophysiology of delirium.

The CONFUSED study aims to extend beyond these approaches by integrating multiple layers of omics data—proteomics, transcriptomics, and epigenetics—with detailed clinical variables. This integrative, multimodal approach allows for the identification of candidate biomarker signatures and mechanistic pathways associated with POD, which cannot be captured by single-omics or clinical-only models. Advanced ML techniques, including feature selection, regularization, and nested cross-validation, are applied to ensure robustness and interpretability of exploratory predictive patterns.

While this study does not yet provide a systematic performance comparison with existing POD prediction models, it is designed to generate hypotheses and candidate signatures that can inform future external validation studies. By combining diverse molecular and clinical data with interpretable ML, the CONFUSED study seeks to provide incremental value in understanding POD risk and to lay the groundwork for the development of more comprehensive and mechanistically informed predictive models.

### Dissemination Plan

The results of the CONFUSED study will be disseminated through peer-reviewed scientific publications and presentations at national and international conferences in the fields of anesthesiology, perioperative medicine, and neurocognitive research. In addition, the study findings will contribute to ongoing research collaborations and may support the development of future multicenter studies, focusing on biomarker-based prediction and prevention of POD.

## Results

### Overview

The study was registered in the German Clinical Trials Register (DRKS00033854) on March 18, 2024. Patient recruitment commenced in January 2024 and is ongoing at the time of manuscript submission (Table 2). As of now, 135 of the approximately planned 200 to 300 patients have been enrolled, corresponding to approximately two-thirds of the target sample size. Sample collection and laboratory analyses are ongoing. Enrollment is proceeding according to the projected timeline (Table 1), and no major protocol deviations have occurred to date. The first results are expected in July 2026.

**Table 2. T2:** Timeline of the study.

Item	Details
Initial ethical approval	Approved in May 2023
Funding date	Funded in January 2023
Ethical approval amendment	Approved in March 2024
Trial registration	Registered in the German Clinical Trials Register (DRKS00033854) on March 18, 2024
Start of recruitment	Recruitment started in January 2024
End of recruitment	Recruitment is expected to be completed in December 2026
Sample size status	As of February 2026, a total of 135 participants have been enrolled
Data collection period	Data collection is planned from April 2024 to March 2027
Laboratory analyses	Laboratory analyses commenced in February 2026
Statistical analysis	Statistical analysis is scheduled to begin in July 2026
Expected publication	First results are expected to be published in Spring 2027

Biospecimen collection at all 4 predefined perioperative time points is ongoing. Sample processing, including initial proteomic and transcriptomic preparation steps, has been initiated in parallel with recruitment to ensure standardized handling and storage conditions. Comprehensive laboratory analyses are currently underway.

Data cleaning and database validation procedures are being performed continuously. Final data lock is anticipated after the completion of recruitment. Statistical analyses, including integrative multiomics evaluation and the development of predictive models, began in January 2026. First results are expected in March 2026, with dissemination through peer-reviewed publications planned thereafter.

### Trial Status

The first patient was recruited on January 15, 2024. The inclusion of participants is ongoing and is expected to continue until November 2026. The first results are expected in July 2026. The trial protocol and statistical analysis plan can be accessed through the corresponding author.

## Discussion

### Principal Findings

The CONFUSED study is designed to improve the prediction and understanding of POD by integrating multimodal molecular data with detailed clinical information. By combining proteomic, transcriptomic, and epigenetic analyses with perioperative clinical variables, the study aims to identify biomarkers and molecular signatures associated with the development of POD. We anticipate that this integrative approach will enable the identification of biological pathways involved in delirium pathogenesis and support the development of predictive models that may help identify patients at increased risk for POD.

The application of ML techniques to multimodal datasets may further enhance predictive performance compared with traditional statistical models. Ultimately, the findings of the CONFUSED study may contribute to a better understanding of the biological mechanisms underlying POD and support the development of personalized prevention strategies in perioperative medicine.

### Comparison With Prior Work

Previous studies investigating biomarkers of POD have primarily focused on individual biomarkers, such as inflammatory cytokines, neurodegenerative markers, or selected genetic variants. While these approaches have provided valuable insights into potential mechanisms, their predictive performance has often been limited due to the complex and multifactorial nature of delirium.

Recent advances in high-throughput molecular technologies have enabled the investigation of complex biological processes using multiomics approaches. However, studies integrating proteomic, transcriptomic, and epigenetic data in the context of POD remain scarce. The CONFUSED study aims to address this gap by applying a comprehensive multiomics strategy combined with advanced data integration methods. This approach may allow for the identification of novel biomarker panels and biological pathways that cannot be detected using single-omics analyses alone.

The application of AI in medical research has the potential to revolutionize our approach to complex conditions, such as POD. POD, a prevalent and challenging complication following surgery, is characterized by acute cognitive disturbances and fluctuating consciousness [21]. Despite substantial research efforts, the prediction and diagnosis of POD remain difficult due to its multifactorial nature and variable clinical presentation [22,23]. Recent advances in OMICs research combined with AI offer promising solutions to these challenges by enabling more accurate and comprehensive predictive modeling [24].

POD is influenced by a range of factors, including patient age, preexisting cognitive impairment, type of surgery, anesthesia, and inflammatory responses [11]. Traditionally, predicting POD has relied on clinical assessment tools and risk scores, which are often inadequate due to their subjective nature and the heterogeneity of delirium symptoms [4]. Omics data, including genetic, epigenetic, proteomic, and metabolic indicators, offer valuable insights into the biological processes underlying POD. For example, inflammatory proteins such as C-reactive protein and IL-6 or high mobility group box 1 have been linked to the increased risk of delirium [25]. Genetic variants and epigenetic modifications, such as changes in DNA methylation, also contribute to individual susceptibility [26].

### Strengths and Limitations

The CONFUSED study has several strengths. First, it employs a prospective observational design with standardized perioperative data collection and systematic delirium assessments using validated instruments (CAM and CAM-ICU). Second, blood samples are collected at multiple perioperative time points, enabling the investigation of dynamic molecular changes associated with the onset and progression of delirium.

Third, the study integrates multiple layers of molecular data, including proteomics, transcriptomics, DNA methylation, and genetic polymorphisms. This multiomics approach provides a comprehensive view of the biological processes involved in the delirium development. Finally, the application of ML methods for data integration and predictive modeling may improve the identification of clinically relevant biomarker signatures.

Several limitations should be considered. First, the study was conducted at a single center, which may limit the generalizability of the findings to other clinical settings or patient populations. Second, although the planned sample size is sufficient for exploratory analyses, validation in independent cohorts will be necessary to confirm the predictive performance of the identified biomarkers and models.

Third, the high dimensionality of multiomics data combined with a relatively moderate sample size may increase the risk of overfitting in predictive modeling. To address this challenge, appropriate statistical methods, cross-validation strategies, and feature selection approaches will be applied. Finally, while peripheral blood samples provide valuable information about systemic biological processes, they may not fully capture neurobiological mechanisms occurring within the central nervous system.

Other challenges should be considered. Privacy and security concerns, the need for extensive and diverse datasets, and the complexity of translating AI findings into clinical practice are notable hurdles [27-29]. While AI can identify associations and patterns, understanding the underlying mechanisms of POD and establishing causality requires further research.

Future directions should focus on improving the interpretability of AI models, integrating them into clinical workflows, and considering ethical aspects. Collaborative efforts between data scientists, clinicians, and researchers are essential to validate AI-driven predictive models and ensure their successful application in clinical settings. By overcoming these challenges, AI has the potential to significantly improve the accuracy of POD prediction and facilitate personalized interventions, ultimately improving patient outcomes and reducing the burden of POD. With regard to cost-effectiveness, a formal health-economic analysis lies beyond the scope of this protocol study, but several considerations are relevant. First, the preoperative clinical model relies exclusively on routinely collected clinical data and requires no additional laboratory analyses, thereby incurring no additional diagnostic costs. Second, POD is associated with a well-documented economic burden, including prolonged hospitalization, higher rates of institutionalization, extended mechanical ventilation, and long-term cognitive decline. Targeted nonpharmacological prophylaxis initiated following early identification of high-risk patients has been shown in randomized trials to reduce POD incidence and shorten hospital stays, yielding downstream cost savings that are likely to outweigh the costs of screening. Third, the full proteomic and transcriptomic workup performed in this study is explicitly designed to identify a focused panel of high-yield biomarkers, which is anticipated to inform the development of targeted, lower-cost point-of-care assays for future routine clinical implementation, substantially reducing per-patient costs relative to the comprehensive analytical workup performed during the study phase.

